### Interim analyses {21b}

The sample size of this study is 1098. Interim analyses are planned to be conducted at three time points: 1 month after the first patient is enrolled, when 50% of the samples are collected, and when 75% of the samples are collected.

### Methods for additional analyses (e.g., subgroup analyses) {20b}

#### Analysis sets

The enrolled set will consist of all participants who provided informed consent and were added to the study database.The full analysis set (FAS) describes the analysis set, which is as complete and close as possible to the intention-to-treat ideal of including all randomized participants, who have undergone ≥ 1 efficacy assessment, post-randomization.The per-protocol set (PPS) defines a subset of the participants in the FAS who are more compliant with the protocol and have undergone ≥ 1 efficacy assessment, post-randomization. Participants with protocol deviations will be excluded from this analysis.

### Methods in analysis to handle protocol nonadherence and any statistical methods to handle missing data {20c}

In the analysis of the primary outcome measure, missing values within the FAS will be excluded.

The analysis of the primary, secondary, and safety outcome measures will be conducted, based on the intention-to-treat principle. Thus, participants will be analyzed, according to either of the intervention cohorts to which they were randomized, and all participants will be included in the analysis, regardless of whether they were assigned to the intervention or not (the FAS).

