### Outcomes {12}

#### Primary outcome

The primary outcome measure is the comparison of the 48-h postoperative oxygenation index between the two cohorts. This will be derived from arterial blood gas sampling and analysis, in addition to the FiO_2_ 48th h postoperatively.

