### Sample size {14}

This randomized controlled trial aimed to examine the effect of varying intraoperative oxygen concentrations on PPCs. This study is a superiority trial in which the optimal effect threshold has been set. Based on a preliminary experiment, 10 samples were collected each group, and the values of oxygenation index were expressed as mean ± standard deviation: 384 ± 85 mmHg for 40% group and 340 ± 60 mmHg for 80% group. This study was designed as a superiority trial, with a clinically significant difference defined as an increase in oxygenation index by at least 30 (10% of 300 acute lung injure oxygenation index) in favor of 40% group compared to 80% group. The pooled standard deviation was estimated to be 74 mmHg. The sample size required for each group to achieve a significant difference, with a one-sided *α* = 0.025 and *β* = 0.20. The minimum sample size required for each group was approximately 439, with a total of 1098 samples needed for both groups, considering a dropout rate of 20%.

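### The primary analysis deletes participants without a 48-h oxygenation index, yet is described as intention-to-treat with everyone in the FAS included

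*Protocol article*

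**What the plan says.** All references are to the protocol article.

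- **Missing data {20c}, first paragraph:** "In the analysis of the primary outcome measure, missing values within the FAS will be excluded".
- **Missing data {20c}, second paragraph:** the primary, secondary and safety analyses follow intention-to-treat, participants are analysed in the cohort to which they were randomised, and "all participants will be included in the analysis". This set is labelled the FAS.
- **Analysis sets {20b}:** the FAS approaches the ideal of "including all randomized participants, who have undergone ≥ 1 efficacy assessment, post-randomization".
- **Eligibility criteria {10}, rejection criteria:** participants unable to complete the trial are rejected, as are those with certain intraoperative events.
- **Primary outcome {12}:** the oxygenation index at 48 h. "This will be derived from arterial blood gas sampling and analysis, in addition to the FiO_2_ 48th h postoperatively". A participant lacking either component has no primary value.
- **Sample size {14}:** pilot values of "384 ± 85 mmHg for 40% group and 340 ± 60 mmHg for 80% group", a required gain of 30 mmHg, SD 74, one-sided 0.025, 80% power, 439 per group, and 1098 in total after 20% dropout.
- **Statistical methods {20a}:** a linear mixed-effects model with age, gender, BMI, prior SARS-CoV-2 infection, intraoperative variables, centre and group.

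**The concern.** This is a printed rule, so it does not depend on detail that an unseen SAP might hold. Someone with PACU or 24-h oxygen data but no 48-h gas is in the FAS if those data count as an efficacy assessment. One paragraph of {20c} then removes that person from the primary analysis, and the next keeps them in. Under the rejection criteria the same person may not be in the trial at all.

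The rule matters because the outcome is a single arterial sample, and absence of that sample can be related to the lungs. Causes could include death, deterioration, withdrawal for an intervention-related adverse event (a listed withdrawal reason), or a well participant declining the puncture. The model adjusts for baseline and intraoperative variables only, so it cannot correct for selection that works through the postoperative respiratory course. The design also leaves little slack: it is sized on the 14 mmHg by which the pilot difference exceeds the 30 mmHg margin.

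**Working it through.** **1. The plan's own figure.** Net effect = (384 − 340) − 30 = 14 mmHg. n per group = 2 × (1.960 + 0.842)² × 74² / 14² = 438.6, so 439. Total = 878 / 0.8 = 1097.5, so 1098. Both figures reproduce. A difference of 30 would need 96 per group and a difference of 44 would need 45, so the design rests on the 14 mmHg.

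**2. Bias of the complete-case difference.** Let m be the fraction missing in an arm, and g the mean of the observed minus the mean of the missing participants. Then

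bias = m_L × g_L − m_H × g_H.

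Equal fractions with equal gaps give zero bias. At 20% missing per arm, a loss of 7 mmHg (half of 14) needs the gaps to differ by 7 / 0.2 = 35 mmHg (0.47 SD). A loss of all 14 needs 70 mmHg (0.95 SD). At 10% missing per arm, losing half already needs 70 mmHg.

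**3. One rule in both arms.** Assumptions, none of them from the documents except the planning values: normal outcomes with means 384 and 340 and SD 74; all of the 20% dropout consists of missing 48-h values; the log-odds of missingness rise by b for each 74 mmHg of worse oxygenation, identically in both arms; the intercept is set to give 20% missing overall; 549 randomised per arm; no covariate adjustment. Results by numerical integration:

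| b | Missing, 40% arm / 80% arm | Gap g, 40% / 80% (mmHg) | Complete-case difference | Loss, as share of 14 | Power against 30 |
|---|---|---|---|---|---|
| 0 | 20.0% / 20.0% | 0 / 0 | 44.0 | 0 | 80% |
| 0.5 | 17.7% / 22.3% | 35.7 / 35.5 | 42.4 | 1.6 (11%) | 72% |
| 1.0 | 15.9% / 24.1% | 65.1 / 63.3 | 39.1 | 4.9 (35%) | 49% |
| 1.5 | 14.7% / 25.3% | 86.6 / 81.9 | 36.0 | 8.0 (57%) | 26% |

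Check with the formula at b = 1.5: 0.147 × 86.6 − 0.253 × 81.9 = 12.7 − 20.7 = −8.0.

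Power = Φ[(difference − 30) / SE − 1.96], with the SE taken from the participants who remain: 4.99, 4.90, 4.71 and 4.52. At b = 1.0 this is (39.14 − 30) / 4.71 − 1.96 = −0.02, or 49%.

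The bias needs no arm-specific mechanism. Because the arms differ in the outcome, one shared rule removes more participants from the worse arm.

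**4. Against zero.** At b = 1.5, 36.0 / 4.52 is about 8.0 standard errors, so power stays above 99.9%.

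**5. The other direction.** Suppose well participants decline the puncture mainly in the 80% arm, with 20% missing there, g_H = −35 and g_L = 0. The bias is then −0.2 × (−35) = +7 mmHg. If the true difference were exactly 30, the one-sided error would rise from 2.5% to Φ[7 / (74 × √(2/439)) − 1.96] = Φ(−0.56), about 29%. If well participants decline by one shared rule, the difference shrinks instead, by symmetry with step 3.

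**The case against.** The strongest replies are these.

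- **The intention-to-treat sentence may only mean analysis by assigned arm.** That reading is compatible with dropping missing values and softens the conflict. It does not fit the further statement that everyone is included.
- **A reader might infer that the section promises analysis of all randomised participants.** It does not. It promises all participants in the FAS, which is already narrowed to those with at least one efficacy assessment. The firm conflict is over FAS members without a 48-h value.
- **A reader might infer that missing data will wipe out most of the 14 mmHg.** The documents do not show this. Only the steepest slope loses more than half. It implies odds of missingness about 4.5 times higher per SD (e^1.5) and missing participants more than 1 SD worse than observed ones.
- **The 20% is total dropout.** How much of it will be missing 48-h gases is not stated, and some may come from the rejection criteria.
- **Safeguards exist.** Experienced anesthesiologists take the sample within routine ward testing, visits run to day 7, and participants and ward assessors are blinded. These should reduce missingness and make refusal driven by knowledge of allocation less likely. The adjusted model is also valid if missingness depends only on its terms.
- **The power loss presupposes a test against 30 mmHg.** The sample size uses that margin, but {20a} does not restate it for the analysis.
- **Absence of imputation detail is not a defect here**, since a SAP may supply it.

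All of this limits the size of the problem. It leaves the printed deletion rule and its conflict with the stated population in place.

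**Conclusion.** The point holds in this form. Sections {10}, {20b} and {20c} do not agree on who enters the primary analysis, and as written a complete-case result would be reported as intention-to-treat. Deletion can be relied on only if missingness depends on nothing beyond group, centre and the model covariates, or if selection happens to cancel between arms. The first is doubtful for a postoperative blood gas, and the second cannot be planned.

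The size is conditional. Under the assumptions in the working, the loss is 11% to 57% of the 14 mmHg net effect, with power against 30 mmHg of about 72% down to 26%. With arm-specific missingness the bias could be larger or could favour the 40% arm. If the test is against zero, the conclusion on significance hardly moves, but the estimate is still biased and still mislabelled. This should be changed before analysis; it is not evidence that the trial will fail.

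**What to change.** 1. Reconcile the rejection criteria in {10}, the FAS definition in {20b} and both paragraphs of {20c}, so that one rule states who is in the primary analysis and participants are analysed as randomised.
2. Replace the exclusion sentence with a primary analysis under a stated missing-at-random assumption. One option is multiple imputation by arm from baseline variables, centre, and the PACU and 24-h oxygen concentration and duration that the trial already records.
3. Add a delta-adjusted (tipping-point) sensitivity analysis that worsens imputed values step by step, separately by arm, and that covers deaths before 48 h explicitly.
4. Keep the complete-case analysis as a sensitivity analysis, labelled as such.

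The cost is revised wording and some extra programming. No new data and no additional participants are needed.

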### Plans to give access to the full protocol, participant-level data, and statistical code {31c}

The full protocol, participant-level dataset, and statistical code can be reasonably obtained from the corresponding author.

## Oversight and monitoring

### Composition of the coordinating center and trial steering committee {5d}

The trial will follow the principles of the protocol, GCP, and Declaration of Helsinki. The trial steering committee is composed of the principal investigator and the co-investigator. In addition, the trial is supported by a professional contract research organization (CRO) that provides project management and clinical monitoring services.

### Composition of the data monitoring committee and its role and reporting structure {21a}

The Data Monitoring Committee is composed of experienced clinicians and statisticians. Monitors will ensure participant enrollment, review informed consent forms, and verify source data and CRF entries. Moreover, they will regularly supervise and monitor the trial progress, to support the clinical trial site investigators in adhering to the protocol, in addition to meeting regulatory and ethical requirements. The clinical trial site investigator will report any AEs to the PI and IRB of the First Hospital of China Medical University, as per the standard operating procedures and policies of the local independent ethics committee.

### Adverse event reporting and harms {22}

AEs are defined as any unpredictable or adverse clinical outcome related to any medical intervention that occurred during the study period.

In accordance with the GCP guidelines, any AE or SAE will be documented on the CRF of the participant using an AE/SAE CRF. This will include details, including the type, date, onset, severity, relationship to intervention, management, and outcome of the AE or SAE. Closely monitoring for all AEs and SAEs is essential. Prompt treatment should be provided, if necessary, based on clinical discernment. Follow-up on the AE or SAE should continue until the event has completely resolved and the participant’s condition is stable or normal.

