### Withdrawal from study

Participants will be withdrawn from the study, if any of the following circumstances arise:The participant has voluntarily withdrawn consent from the study.Continuing in the trial will may be harmful to the health of the participant.The trial records cannot be completed, and the research investigator regards the participant as no longer able being to continue in the trial.AEs related to the trial intervention occur.Factors posing a risk are considered by the Trial or Advisory Committee.The rationale for a participant’s withdrawal from the study will be documented in the “Withdrawal/Change of Status” table.

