## Assignment of interventions: blinding

### Who will be blinded {17a}

Due to the nature of the study, anesthesiologists will not be blinded to the intervention protocol. Trial participants, outcome assessors, and data analysts will be blinded. To reduce potential bias, data collectors will be divided into two different teams: (1) anesthesiologists on duty in the operating room on the same day, in addition to postanesthetic care unit (PACU) staff, who will participate in the calculation and evaluation of the results, and (2) blinded principal investigator (PI) and co-investigator, statistician, and data collection and outcome evaluation personnel, which includes those who will provide care and evaluate participants in the ward pre- and postoperatively.

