## Data collection and management

### Plans for assessment and collection of outcomes {18a}

Each site will administer anesthesia, according to their institutional guidelines. Medication type, dosing, and additional analgesics administered, as per each site’s anesthesia protocol, will be documented, in detail, in the case report form (CRF). A qualified and experienced anesthesiologist will be required to complete the CRF.

Prior to study initiation, researchers will receive training on the study protocol, according to the principles of GCP for clinical trials.

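### The adverse event definition requires a relation to medical care, so events judged unrelated need not be recorded and some harms may be undercounted

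*Protocol article*

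**What the plan says.** All references are to the protocol article.

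- **Definition.** Adverse event reporting and harms {22} defines AEs as "any unpredictable or adverse clinical outcome related to any medical intervention that occurred during the study period".
- **Recording rule.** The next paragraph of that section says: "In accordance with the GCP guidelines, any AE or SAE will be documented on the CRF of the participant". The details to be entered include "severity, relationship to intervention, management, and outcome of the AE or SAE". The section also calls for close monitoring of every AE and SAE.
- **Withdrawal.** One reason listed under Withdrawal from study is that "AEs related to the trial intervention occur".
- **Who knows the arm.** Who will be blinded {17a} says that "anesthesiologists will not be blinded to the intervention protocol". It puts operating-room anesthesiologists and PACU staff in a team "who will participate in the calculation and evaluation of the results". The second, blinded team includes "those who will provide care and evaluate participants in the ward pre- and postoperatively".
- **Who fills in the form.** Plans for assessment and collection of outcomes {18a}: "A qualified and experienced anesthesiologist will be required to complete the CRF".
- **Use of the data.** The section on nonadherence and missing data {20c} includes safety outcomes in the intention-to-treat analysis by randomised cohort. The auditing section {23} has aggregated AE data fed back after every 100 subjects.

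**The concern.** A safety comparison should start from everything untoward that happened and treat causality as a later, separate judgement. Here the causal judgement comes first. The rule that any AE or SAE is documented reaches only what the definition admits, so it cannot bring back an event that the definition has excluded. An event judged unrelated to medical care leaves no entry, and no later analysis can recover it.

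Two things are at stake. AE and SAE totals may be too low in both arms. If the judgement is made differently in the two arms, the comparison may also be distorted. The background cites conflicting evidence on harm from high FiO2, so a complete harm count is of real interest in this trial.

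**Working it through.** **1. Which events the wording admits.** The definition speaks of any medical intervention. The CRF field speaks of relationship to intervention, most naturally the allocated FiO2. The withdrawal criterion speaks of the trial intervention. Every untoward event then falls into one of three classes:

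| Class | Meets the definition? | Separated by the CRF field? |
|---|---|---|
| A. Related to the allocated FiO2 | Yes | Yes, related |
| B. Related to other care (surgery, anesthesia, drugs), not to FiO2 | Yes | Yes, unrelated |
| C. Judged unrelated to any medical care, e.g. attributed to underlying disease | No | Never reaches the field |

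The definition and the field can therefore coexist: the field separates A from B. Class C is what is lost.

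**2. Which outcomes are exposed.** Pulmonary complications at 7 days and mortality at 30 days are secondary outcomes, listed under Outcomes {12} and modelled under Statistical methods {20a}. Neither carries a relatedness condition. The exposure is limited to the other AEs and SAEs.

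**3. Who would make the judgement.** No section assigns it. For events in the operating room and PACU, the staff present know the arm, and {18a} has an anesthesiologist complete the CRF, so an unblinded judgement is possible there. On the ward, evaluation is by blinded personnel {17a}. Visits to day 7 and telephone follow-up to day 30 are by data collection and outcome evaluation personnel {18b}, whom {17a} lists as blinded.

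**4. What arm-dependent recording could do.** No figure in the article depends on the AE definition. The only input it supplies is the number per arm, which reproduces:

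- Sample size {14}: difference 384 − 340 = 44, less the margin of 30, gives 14; SD 74; one-sided α 0.025; power 0.80.
- n = 2 × (1.960 + 0.842)² × 74² / 14² ≈ 439 per arm. Then 439 / 0.8 = 548.75, rounded up to 549, and 2 × 549 = 1098, as stated.

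The rest is assumed. Let p be the true event rate, equal in both arms, and q the share recorded in an arm. The recorded rate is r = p × q. With n = 549 per arm,

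z = (r_L − r_H) / √{[r_L(1 − r_L) + r_H(1 − r_H)] / n},

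and the chance of a nominally significant false difference in that direction is Φ(z − 1.96).

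Example with p = 20% and recording of 90% versus 80%: r = 0.18 and 0.16; standard error √[(0.1476 + 0.1344)/549] = 0.0227; z = 0.88; chance Φ(−1.08) = 14%.

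| Assumed recording, L / H | Apparent ratio H/L | Chance at p = 10% | p = 20% | p = 30% |
|---|---|---|---|---|
| Equal | 1.00 | 2.5% | 2.5% | 2.5% |
| 95% / 90% | 0.95 | 4.7% | 6.3% | 8.0% |
| 90% / 80% | 0.89 | 8.6% | 14.0% | 20.6% |
| 90% / 70% | 0.78 | 23.0% | 43.9% | 64.4% |

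Swapping the arms gives the mirror image. Equal under-recording lowers the totals but leaves the ratio intact. The table shows what could happen under each assumption, not what is expected.

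**The case against.** The strongest reply is that the condition is very wide. It asks for a relation to any medical care, not to the allocated FiO2. In patients aged 65 or over having laparoscopic surgery of more than two hours, most perioperative events can be tied to surgery, anesthesia or drugs, so class C may be small. Deciding whether an event relates to any care at all also depends little on knowing the FiO2 arm. This stands, and it limits the likely effect.

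It can also be said that the reference to GCP, the call to monitor every AE and SAE, and the separate mention of AEs related to the trial intervention show an intent to record broadly. That is fair as to intent. It shows that AEs unrelated to FiO2 are expected. It does not show that events unrelated to all medical care are recorded, because each of these statements uses the term AE as defined.

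A third reply is that the full protocol or CRF guide may hold the detail. The point does not rest on missing detail, however. The article states a definition, and that definition governs what sites collect.

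A reader might go further and infer that unblinded anesthesiologists screen the safety data. The documents do not support this. The sentence about completing the CRF follows text on anesthetic medication and dosing, it does not assign causality, and evaluation on the ward is blinded.

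**Conclusion.** The point holds as a defect in a stated collection rule. As worded, an event judged unrelated to medical care is not an AE and need not be recorded. This can undercount AEs and SAEs other than 7-day pulmonary complications and 30-day mortality, both in the by-arm safety analysis and in the periodic AE feedback.

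The size is unknown. The document gives no expected AE rate and no basis for the share of events that would be judged unrelated. A reader might take the 14% or 44% in the table (true rate 20%, recording 90% versus 80% or 70%) as the trial's false-positive risk for harm. That is not supported: those values rest wholly on assumed arm-specific recording rates, and the article names no AE endpoint among its modelled outcomes. An arm-dependent distortion is possible for operating-room and PACU events but is not established. Nor is the whole safety comparison affected, since the two main harm outcomes are collected without the condition.

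The change is still worth making, because lost events cannot be recovered and the remedy is nearly free.

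**What to change.** Replace the definition in Adverse event reporting and harms {22} with wording such as: any untoward clinical event from randomisation to the end of follow-up, whether or not considered related to any intervention. Keep relationship as a separate recorded field, and say that it means relationship to the allocated FiO2. State that between-arm safety tables are based on all recorded events, with related events shown as a subset if wanted.

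The cost is one sentence in the protocol and the matching line in the CRF instructions. The downside is that slightly more events will be recorded on the existing forms.
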